## 10.6 Adverse Event Reporting

All adverse events and incidents associated with the procedures of this study will be reported within the time frames required by the appropriate Institutional Review Boards. Appropriate action will be taken to address any adverse events or incidents.

## 10.7 Study Withdrawal and Discontinuation

The study may be discontinued at any time by the NIH. Study participants will be informed though the process of informed consent that they may withdraw from the study at any time for any reason. Participants may be withdrawn from the study by the site Principal Investigators if they are found to have:

- An obvious psychological/psychiatric disorder that would invalidate the informed consent process, or otherwise contraindicate participation in the study; or
- Any other condition which in the opinion of the study site Principal Investigator will interfere with achieving the study objectives. In such cases the Principal Investigator will review the reasons for withdrawal with the study team prior to participant notification. The Principal Investigator may decide to include data collected prior to participant withdrawal in study analyses.

## 10.8 Incentives for Participation

Participants will be reimbursed TSH 10,000 (~$6.25) for the transportation costs incurred to travel to the interview site and for the time that they spent in transit to and during the interviews. This includes participation in the baseline behavioral and biological assessment, and the 12 and 30 month follow-ups. Health Leaders nominated from camps will receive TSH 10,000 (~$6.25) for each day present of the 5-day training. Likewise, all camp members eligible for the microfinance component will receive TSH 10,000 (~$6.25) for each day present during the business and entrepreneurship training.

## 10.9 Linkages to Care

All stages of this trial are planned in the context of recognized ethical principles for protecting human participants in international research. Participants who test positive for an STI during the baseline or 30 month assessment will receive free treatment and will have access to a trained psychologist if desired. Participants who are symptomatically positive for an STI will also be offered free treatment.

In order to track access to the above interventions, we will make a list of health facilities (public, nongovernmental, private) in each community and will determine which types of HIV-related prevention and treatment interventions are available in each facility by interviewing facility managers at baseline and updating the list annually. This activity will be the responsibility of the Study Site Project Director at each site.

## 10.10 Inclusion of Women

Because men are the primary targets in this study, we have focused on them in the details of this protocol. However, women are included as participants in all stages of this trial and all will be able participate in behavioral assessments. Diagnostic STI tests will be completed with men only, and women will be offered a syndromic STI assessment and free care if the assessment is positive. Both men and women will have access to a trained psychologist should they desire counseling after a positive assessment. Female members of intervention camps will be eligible for microfinance and to be elected as a Camp Health Leaders. This strategy is aimed to maintain the leadership and social support inherent in camps. While we acknowledge that the risks of physical and social harms are greater for women than men, we do not believe that the exclusion of women from the trial based on this potential risk could be justified.

## 10.11 Inclusion of Minorities

This cluster-randomized trial will be conducted in urban camps within four wards of Dar es Salaam Tanzania. All study participants are Black African. The intervention component will be applied to all members of camps assigned to this condition. All camps verified in these four wards that meet inclusion criteria (size, length in existence, and safety) are eligible for participation. All camp members meeting individual criteria (age, length of membership, plans to remain the city for 30 months, willingness to provide locator information) will be eligible for inclusion in the study.

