# PROTOCOL SUMMARY

**Purpose:** The purpose of this study is to determine whether men in camps randomized to receive a microfinance and health leadership intervention have a lower incidence of sexually transmitted infections (NG, TV, CT) and report perpetrating less physical or sexual violence against female sexual partners as compared to men in camps not randomized to receive the intervention.

**Design:** Cluster-randomized trial.

**Study Population:** Young men ages 15 or older that are members of camps (social groups) in Dar es Salaam, Tanzania.

**Study Size:** 1249 male camp members

**Intervention:** 60 eligible camps will be randomized in to either a microfinance and health leadership intervention or a control condition. Eligible members in the intervention camps will be able to participate in intervention activities.

**Duration and Follow-up:** This a 5 year cluster-randomized study. Behavioral data will be collected at baseline, 12 months, and 30 months after intervention. Biological data will be collected at baseline and 30 months.

**Primary Objectives:** To determine whether men in camps randomized to receive a microfinance and health leadership intervention have a lower prevalence of sexually transmitted infections (NG, TV, CT) and report perpetrating less physical or sexual violence against female sexual partners as compared to men in camps not randomized to receive the intervention.

**Primary Endpoints:** Incidence of STIs (NG, TV, CT) and perpetration of sexual violence against female sexual partners.

**Secondary Endpoints:** HIV risk and protective behaviors including: gender equity, alcohol and drug use, sexual relations and risk behavior, uptake of HIV counseling and testing; unprotected sexual intercourse; consistent condom use; delay of sexual debut; number of sexual partners, and sexual concurrency.

**Mediators**: In the event that program effects are identified, the degree to which the following mediate the multi-level intervention on STI and gender-based violence: hope, future orientation, social cohesion, collective efficacy, social support, emotional distress, sexual networks, social support and social influence.

**Qualitative:** Qualitative interviews with study participants will add contextual data for understanding various aspects of participant beliefs, attitudes, and behaviors towards endpoints measured.

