### 4.1.4 Camp Random Selection

60 camps will be randomly selected in to the study, and later assigned in to one of two conditions – intervention or control. Due to the density of camps within wards and the contiguous nature of some camps, measures will be taken to minimize contamination of potential intervention and control camps before random assignment. The following steps will be taken during the random selection of camps.

1. Local staff will group geographically contiguous camps posing a threat to potential contamination. Eligible camps will be mapped by GPS coordinates on a street layout of the four wards to facilitate grouping. Groups will contain up to 6 camps, individual isolated camps will not need to be put in a group.
2. Groups will be selected for inclusion in the study using probability proportionate to size. Thus, groups with numerous camps of large membership have the potential to be selected more than once.
3. Simple random selection of camp(s) will be completed among camps in each group selected in to the study. Camps from the same group randomly selected in to the study will necessarily receive the same condition during the condition assignment phase.

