### 5.3.1 Nomination Process

Twenty percent of the total number of members at each camp will be nominated in to a Health Leadership role (n = Camp members on roster x 0.20). Nomination will occur at each camp separately when at least 50% of camp roster members are present. After discussing attributes of leaders, each camp member in attendance will nominate confidentially up to 3 leaders in their camps with these qualities. Leaders identified will then be approached and asked if they are interested in being trained as peer leaders for their camp.

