**Loan Acquisition**

We will keep a roster for all camp members eligible for the microfinance intervention (completed baseline survey), and compare this to the total number of individuals who fulfill requirements and access loans.

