| Q007 | How often would you say you come to camp X? | EVERY DAY  SEVERAL TIMES A WEEK  ONE TIME PER WEEK  COUPLE TIMES A MONTH  ONE TIME PER MONTH  LESS THAN ONCE A MONTH | 1  2  3  4  5  6 | **END**  **END**  **END** | ELIG7 |
| Q008 | Are you a member of any other camps? | NO  YES | 0  1 | **Q012** | ELIG8 |
| Q009 | What are the names of these other camps?  *Note: If participant is a member of more than 2 other camps, separate these camp names with a comma.* |  |  |  | ELIG9 |
| Q010 | [DO NOT READ OUTLOUD]  By looking at the list of 60 study camps, determine whether participant is a member of another study camp. Is the participant a member of another study camp? | NO  YES | 0  1 | **Q012** | ELIG10 |
| Q011 | I see that you are also a member of camp X. Which of these camps would you consider to be your PRIMARY CAMP? By primary camp, I mean you spend more time in this camp than any other camp. | This Camp  Other Camp |  | **END** | ELIG11 |
| Q012 | Have you answered these types of questions and have you previously provided a sample of your blood and urine to our study staff? | NO  YES | 0  1 | **END** | ELIG12 |
| Q013 | Do you plan to live in Dar es Salaam for the next 30 months? | NO  YES | 0  1 | **END** | ELIG13 |
| Q014 | Are you willing to provide a phone number and contact information for two family members or close friends so that study staff can contact you in the future? | NO  YES | 0  1 | **END** | ELIG14 |

*Interviewer:*

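### A man enrolled under a control camp may be nominated and trained as a Camp Health Leader in a second, intervention camp, because access follows camp membership and not enrolment

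*Protocol*

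**What the plan says.** **Enrolment.** The screener in Appendix D, Section 0, asks about membership of other camps (Q008-Q009). At Q010 it tells the interviewer: "By looking at the list of 60 study camps, determine whether participant is a member of another study camp". A man in two study camps names his primary camp at Q011. If it is the other one, the interview ends; otherwise screening continues under this camp. He is not excluded from the trial. Section 4.3 has each camp leader list every member on the roster.

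**Access to the intervention** is worded in four ways:

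- Section 10.11: "The intervention component will be applied to all members of camps assigned to this condition".
- Section 5.3.1, on leaders: "Twenty percent of the total number of members at each camp will be nominated in to a Health Leadership role". The number is computed from the roster, and "each camp member in attendance will nominate confidentially up to 3 leaders in their camps with these qualities".
- Protocol Summary: "Eligible members in the intervention camps will be able to participate in intervention activities".
- Section 7.6.2, Loan Acquisition: "We will keep a roster for all camp members eligible for the microfinance intervention (completed baseline survey".

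**Contamination.** Section 4.1.4 states that "measures will be taken to minimize contamination of potential intervention and control camps before random assignment". Contiguous camps thought to pose a threat are grouped, up to six to a group, and selected camps from one group receive the same condition.

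**The concern.** Two rules are in play and they use different keys. The screener fixes the camp under which a dual member is surveyed and analysed. The access rules ask only whether he is a member, or an eligible member, of an intervention camp. No passage says what a man enrolled under a control camp may receive in his second camp.

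Such a man could receive leader training, and possibly business training and loans, while counted as a control. That would pull both primary comparisons towards no difference. A dual member trained as a leader might also carry the messages into his control camp, since peer diffusion is the mechanism the intervention relies on (Sections 1.4.2 and 5.3).

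**Working it through.** **Step 1. Follow one man through the rules.** His primary camp is control, his second camp is an intervention camp in a different group, and he attends both every week.

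| Rule | Does it bar him in the second camp? |
| --- | --- |
| Participant eligibility (4.3.1) | No. The list covers age, three months' membership, weekly visits, residence and contacts. It has no primary-camp criterion. |
| Q011 skip (Appendix D) | It ends the survey in the non-primary camp. It does not mention training, loans or leadership. |
| Leader nomination (5.3.1) | No. The pool is the roster, and enrolment elsewhere is not checked. |
| Section 10.11 | No. It covers all members. |
| Protocol Summary and Loan Acquisition (7.6.2) | Unclear. He has completed a baseline survey, but under the other camp. |
| Grouping (4.1.4) | Only if both camps are in the same group. |

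The leader route is open on the text. The loan route is unsettled.

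**Step 2. The plan's own figure.** Section 9.1.1 gives a detectable odds ratio of 0.65 for violence perpetration with 2808 men in 54 camps (54 x 52 = 2808), 80% power, two-sided alpha 0.05, 20% attrition and design effects up to 2.3. With 52 x 0.8 = 41.6 men per camp and an ICC of 0.032, the design effect is 1 + 40.6 x 0.032 = 2.30, which agrees. The control rate behind 0.65 is not stated, so that figure can be neither confirmed nor refuted. At an assumed 25% control rate the detectable odds ratio is 0.644, close to it. This point does not dispute the figure.

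**Step 3. Dilution, as an illustration.** Let c be the share of controls who cross over and get the full effect; c is an assumption. The observed control rate is p0 - c(p0 - p1).

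Assumed p0 = 0.25, true odds ratio 0.65:

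- Intervention odds: 0.3333 x 0.65 = 0.2167, so p1 = 0.178 and the difference is 0.072.
- c = 5%: control rate 0.25 - 0.05 x 0.072 = 0.2464, odds 0.3270, observed odds ratio 0.2167/0.3270 = 0.66.
- c = 10%: control rate 0.2428, odds 0.3207, observed odds ratio 0.2167/0.3207 = 0.68.
- Sample inflation 1/(1-c)^2: 1/0.95^2 = 1.11 and 1/0.90^2 = 1.23.

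Assumed p0 = 0.41, the lifetime figure from the preliminary survey (Section 1.7): the observed odds ratio is 0.663 at 5% and 0.677 at 10%.

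**Step 4. Power at p0 = 0.41**, by the two-proportion normal approximation. Effective men per arm:

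- 2808 men: 2808 x 0.8/2/2.3 = 488.
- 1249 men (Protocol Summary): 1249 x 0.8/60 = 16.65 men per camp, design effect 1 + 15.65 x 0.032 = 1.50, and 1249 x 0.8/2/1.50 = 333.

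| c | Odds ratio | Power, 2808 men | Power, 1249 men |
| --- | --- | --- | --- |
| 0% | 0.650 | 0.90 | 0.76 |
| 5% | 0.663 | 0.87 | 0.72 |
| 10% | 0.677 | 0.83 | 0.67 |

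**Step 5. How plausible is 5-10%?** Assume dual members' second camps split evenly between arms, and that they are nominated at the 20% rate of Section 5.3.1. Then 5% crossover through leadership alone needs 0.05/(0.5 x 0.2) = 50% of control men to belong to a second study camp, and 10% needs all of them. If every cross-arm dual member crossed over by some route, 5-10% would still need 10-20% dual membership.

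**The case against.** A reader might infer that the plan delivers the intervention, loans included, to men analysed as controls. The text does not support that. It leaves a gap and directs nothing of the kind. The Section 10.11 sentence stands under the inclusion of minorities and is a general statement of coverage. The Protocol Summary speaks only of eligible members, and the loan roster can naturally be read as requiring a survey completed as a member of that camp. That the man stays on his second camp's roster after Q011 is also an inference, since no passage says what happens to the roster. All this stands, and it is why the loan route is called unsettled here.

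The grouping is a real safeguard: dual members within one group cannot cross arms. What remains is men in two study camps, in different groups and opposite arms, with the control camp as primary. The 20% quota makes a large crossover through leadership alone unlikely (Step 5).

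Some loan crossover would show in the survey, since Q1615 and Q1620 name the microfinance institution as a source of funds. These items do not separate a trial loan from an ordinary one by the same lender, and they do not record leader training.

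Removing men from nomination alters a peer-driven process slightly, and a dual member can still talk to leaders when he visits. Both points stand as limits of the fix. Neither answers the missing rule.

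**Conclusion.** The concern holds as a gap in the rules. The protocol permits a man enrolled under a control camp to be nominated and trained as a Camp Health Leader in a second, intervention camp, and leaves open whether he may borrow there. The passages on access do not agree with one another.

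The size cannot be determined from the protocol and is probably small. The shift from 0.65 to about 0.66-0.68 rests on assumed crossover of 5-10%, full effect in those men, no onward spread in the control camp, and an assumed control rate of 25% or 41%. Under the 41% assumption, 10% crossover costs about 7 points of power with 2808 men and about 9 with 1249. The direction is towards no difference. No stated number in the protocol is shown to be wrong. The gap is worth closing because the plan already treats contamination as a threat and already collects at screening what is needed to prevent it.

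**What to change.** 1. State in Sections 5.2 and 5.3.1 that business training, loans and Camp Health Leader nomination follow the primary camp recorded at Q011, so that a participant enrolled under a control camp is not eligible for them in an intervention camp. Leave such men off that camp's nomination list and out of its 20% count.
2. Reconcile the Protocol Summary, Section 5.3.1, the Loan Acquisition entry in Section 7.6.2 and Section 10.11 with this rule. In particular, say under which camp the baseline survey must have been completed.
3. Match the dual members flagged at Q009-Q010 against the training, leader and loan rosters, and report the number crossing over by arm. If activities have already begun, this step still measures how much crossover occurred.

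**Cost.** A few sentences and a roster check on data already collected. A small number of dual members could not borrow or lead in their second camp during the trial. Informal exposure from visiting that camp would remain.

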## 10.12 Inclusion of Children

This trial targets young, urban men in Dar es Salaam, Tanzania. All phases of this trial require a minimum age of 15 to participate. This cut-off was chosen to maximize inclusion of young men who are newer in developing patterns of sexual relationships, to capture the range of men who are members of camps, and to determine how the intervention works with different aged men

# 11. LABORATORY SPECIMENS AND BIOHAZARD CONTAINMENT

## 11.1 HIV Testing

As HIV and other blood-borne infectious agents can be transmitted through contact with contaminated needles/lancets, blood, or blood products, universal precautions will be employed by all personnel involved in this study. Safety standards reflect those required by the Occupational Safety and Health Administration (OSHA) and recommended by the CDC. Policies for biohazard prevention and response, provision of postexposure prophylaxis for staff members having possible exposures to HIV-infected body fluids, and disposal of biological/hazardous waste will be followed. Good Clinical Practices will be followed by all nurses collecting biological specimens to ensure the safety of participants and self.

# 12. ADMINISTRATIVE PROCEDURES

## 12.1 Community Preparedness and Involvement

The study will conduct specific community preparedness activities in all wards being considered for inclusion in the research. The community preparedness activities will commence prior to communities’ randomization into the study, and will continue throughout the course of the study, with the goals of preparing communities for possible involvement in the study, maintaining constructive relationships with the communities over the course of the study, and ensuring that the research is responsive to community expectations and needs.

The first step in preparing for the study is for field staff to introduce themselves and the study concept to stakeholders. Prior to any data collection the Research Coordinator will meet with local ward officials to explain the study and how recruitment will occur. Initial data collection to identify and verify camps in the wards will be coordinated with these local ward officials. The Research Coordinator will also be responsible for explaining the study to camp leaders contacted for verification and provide updates on procedures for random selection and assignment.

After getting to know the communities socially and geographically, the study team can begin to build the Community Advisory Board (CAB). For this study the CAB will be composed of local government leaders, camp leaders, and parents of camp members. All participating wards and camps will be represented in the CAB. The primary purposes of the CAB are to provide the study team with input on plans of study implementation and serve as a community liaison between researchers and the community. As CAB members become more familiar and knowledgeable with our staff and project, there will be greater participation on study-specific issues where members may have a range of suggestions, concerns, and advice to offer. CAB meetings will be held periodically throughout the life of the project to discuss project progress.

Communities will be actively prepared for the initiation of the study. This will include ensuring that the randomization process is as transparent as possible. Extensive explanation of the community randomization process will be conducted with the CAB. The concepts underlying randomization and its importance in interpreting the study results will be elucidated. The results of the randomization will be provided to the CAB in a clear manner, and any questions or concerns regarding the results for the randomization will be addressed promptly by study personnel.

## 12.2 Study Coordination

The University of North Carolina at Chapel Hill will serve as the Operational Coordinating Center. In this capacity, UNC will be responsible for convening the study team on conference calls, setting agendas and meetings, recording and distributing minutes, setting the study timeline, interacting with NIMH, preparing the study protocol, and ensuring that the relevant IRB regulations are followed.

The Muhimbili University of Health and Allied Sciences will be responsible for coordinating and implementing all phases of the study. This will include community engagement, trainings, data collection, data transfer, and intervention implementation and follow-up. During critical implementation phases throughout the course of study the UNC PI or study coordinators will travel to Tanzania to work with the field based study team. This will allow them to visit the communities at each of the sites and discuss and collaborate on arrangements for the study from the vantage point of the actual experience of those sites.

